#### The movements in the free environment:

Will be analysed for:

- detection and exclusion of the passive movements (in comparison with the diary)
- definition of a threshold to detect the periods of inactivity / activity
- determination of the percentage of inactivity / activity periods during the day
- activity periods:
  - detection of the passive movements
  - recognition of a particular task with the help of recordings in the controlled environment (ex: teeth brushing, eating, getting dressed).
- realization of a histogram of distribution of the module values of the acceleration and the module of the angular speed
- definition of the distribution of the accelerations x, y, z to analyse the proportion of the contra gravity acceleration
- comparison of acceleration profiles between every subject to observe the coherence between the functional abilities measured in the controlled environment and the measured activity at home.
- comparison within a days and within a week.

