#### **6. THE INCLUSION CRITERIA**

The patients have to satisfy the following criteria:

- older than ten years old
- confirmed diagnosis of a neuromuscular disease (DMD, SMA) by the genetics or by the muscular biopsy
- not able to walk ten meters without outside human help or cane
- able to sit on a wheelchair during at least three hours
- assigned to a social security system
- signed informed consent

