## 8.1. GENERAL COURSE OF THE STUDY

During their first visit, the patients will meet a medical investigator who will give them an information form for reading and will answer their questions. The informed consent will then be collected and medical data will be written down (weight, size, pathology, Brooke and Walton score, and medical-surgical history). The patients will receive all the necessary information regarding the use of the **Actimyo** device (see below). The patients will be then asked to perform series of tasks in upper limbs, the accelerations and angular velocities will be recorded by the **Actimyo** device. All the tests take about three hours. This first phase is intended to correlate the measurements with the results validated in controlled environment.

Thereafter, the patients will be trained to wear the Actimyo device for two next weeks. The recordings will be only during the day, the batteries of the device must be recharged every night. The patient will be asked to remove the device when having a bath in order to avoid immersion. In all, about fifteen hours of usual activity will be recorded daily in subject's environment. Throughout this period, the patient will maintain a diary of his daily activities, making notes by themselves or by a close relative, the time of the beginning and the end of the activity (for example brushing teeth, eating, using the computer, and dressing). [Appendix 1]

In two weeks, the patients will return to the centre with the **Actimyo** device and the same series of tests will be recorded.

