### **Using ActiMyo outside the Institute of Myology**

The patient will leave the Institute of Myology, taking the Actimyo device (a sensor placed on the wrist and the otherone placed on the wheelchair). Beforehand he will receive a full explanation of its functioning. At the end of the day, Actimyo will be removed from the wrist and will be connected to USB port of patient's PC for charging. The next day, before starting his usual activities, Actimyo will be fasten to the wrist by the patient himself or by someone from his family. The new recording begins automatically. The box fastened to the wheelchair will be switched on (in the morning) and off (at the end of the day) by pressing a button. The patient will have a little diary that will be given to him where he will be able to write down the time and the date of the

beginning and the end of an activity (like brushing his teeth, eating, using the computer, getting dressed (see Appendix 1).

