## **10. DATA COLLECTION**

The evaluations will be conducted by a physiotherapist, a psychomotor therapist or a trained medical doctor. An information form will be used to write down the results of the tests mentioned above. In addition, an examiner will write down the passive movements (induced by a doctor or a parent) during an assessment day.

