### **18.2. DATA ANALYSIS**

#### The movements in the controlled environment

For every patient, the connection between the functional abilities (the scores) and the measured accelerations, or any other susceptible measurements to summarize the activity of the subject will be used. We will use to make a linear correlation.

The reliability of the measurements of the tests according to which each patient got the same result will be estimated according to ICC method (the correlation of intraclass correlation coefficient).

Besides, two- days' evaluation will allow assessing the ability of the program analysis to determine the passive movements (noted by one of the examiners).

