## 22. APPENDIX

### 22.1 Appendix 1

NOM :

PRENOM :

DATE :

Durée d'utilisation ACTIMYO :.....heures

J( )

Main : .....

| HEURES       | MISE EN
PLACE
D'ACTIMYO
(heure) | ACTIVITÉS DE LA
VIE
QUOTIDIENNE
(toilette, repas,
habillage,
loisirs...)
(heure) | COMMENTAIRES | RETRAIT
D'ACTIMYO
(heure) |
|---------------------|----------------------------------------------------|-----------------------------------------------------------------------------------------------------------------|---------------------|------------------------------------------|
| 7h-8h        |                                                    |                                                                                                                 |                     |                                          |
| 8h-9h        |                                                    |                                                                                                                 |                     |                                          |
| 9h-10h       |                                                    |                                                                                                                 |                     |                                          |
| 10h-
11h |                                                    |                                                                                                                 |                     |                                          |
| 11h-
12h |                                                    |                                                                                                                 |                     |                                          |
| 12h-
13h |                                                    |                                                                                                                 |                     |                                          |
| 13h-
14h |                                                    |                                                                                                                 |                     |                                          |

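### The diary named as comparator for excluding passive movements at home does not ask who moved the arm or whether the patient was in the wheelchair

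*Protocol*

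**What the plan says.** Section 18.2, under the free-environment heading, lists as its first analysis step "detection and exclusion of the passive movements (in comparison with the diary"). It lists detection of passive movements again under activity periods, this time without mentioning the diary.

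Section 8.1 asks the patient or a close relative to note "the time of the beginning and the end of the activity (for example brushing teeth, eating, using the computer, and dressing"). Section 9, on use outside the Institute, gives the same instruction: "beginning and the end of an activity (like brushing his teeth, eating, using the computer, getting dressed (see Appendix 1"). The Appendix 1 sheet has one row per hour from 7h to 22h. Its columns are the hour, device put on, daily-life activities (washing, meals, dressing, leisure), "COMMENTAIRES", and device removed. The sheet's header adds the date, the hand and the duration of use.

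For the controlled setting, section 10 provides that "an examiner will write down the passive movements (induced by a doctor or a parent) during an assessment day". Section 18.2 uses those notes for "assessing the ability of the program analysis to determine the passive movements (noted by one of the examiners"). At home the system consists of "a sensor placed on the wrist and the otherone placed on the wheelchair".

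**The concern.** A comparator has to contain the thing being compared. To check whether the program has correctly removed passive movement at home, one needs an independent record of when the arm was moved by someone else. The diary records what was going on and when, but not who supplied the movement. Dressing looks the same on the sheet whether the patient or a carer did it, yet these two cases are what the exclusion step has to separate.

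Pré-Acti is a validation study (section 4) of a measure intended as a primary outcome for later trials (section 1). Section 18.2 derives the percentage of active time at home and looks for coherence between home activity and functional ability in the controlled setting. Both depend on passive movement having been removed. If weaker patients receive more help, which is plausible but not stated in the protocol, the error would be related to function and could weaken that coherence. With 10 patients, a few misclassified profiles could matter.

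The diary sheet is part of this protocol, so a later analysis plan cannot recover what the sheet did not collect.

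**Working it through.** The check is mainly a comparison of texts. The protocol gives no figure for this point that could be reproduced.

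**Step 1. What the exclusion needs, against what each source supplies.**

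| Source | Where | Who moved the arm? | In or out of the chair? | Covers home days? |
|---|---|---|---|---|
| Diary instructions | Sections 8.1 and 9 | Not asked | Not asked | Yes |
| Diary sheet | Appendix 1 | No field; free comments only | No field; free comments only | Yes |
| Examiner notes | Section 10 | Yes | Not stated | No |
| Wheelchair sensor | Section 9 | Not by itself | No occupancy log; switched on in the morning and off at the end of the day | Yes |

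No source that covers the home days is set up to record whether a movement was passive.

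**Step 2. Can the assessment-day test stand in for a home reference?** Only in part. The tasks scheduled in section 8.2 are performed by the patient. Washing and transfers are not scheduled, and dressing is reduced to buttoning a jacket whose sleeves are already on (section 9). Examiners note whatever passive movement occurs, but the programme does not include the care episodes at home in which a carer is most likely to move the arm. Section 18.2 also plans to recognise dressing as a task within activity periods, so an unlabelled carer-assisted episode could be kept as activity.

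**Step 3. Can the comments column stand in?** Not as designed. It carries no prompt about passive movement. A blank cell may mean that nothing passive happened or that nobody thought to write it down.

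**Step 4. Size, on assumed values only.** The protocol gives no amount of passive movement, no detection accuracy and no activity threshold. The one usable input is about 15 hours of recording a day (section 8.1), which agrees with the 15 hourly rows on the sheet: 15 × 60 = 900 minutes. If all carer-moved arm time went undetected, its share would be minutes ÷ 900:

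- 30 min/day (assumed): 30 ÷ 900 = 3.3%
- 60 min/day (assumed): 60 ÷ 900 = 6.7%
- 120 min/day (assumed): 120 ÷ 900 = 13.3%

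Any share that the program detects lowers these figures in proportion.

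**The case against.** The strongest reply is that the diary is not the only safeguard. Section 18.2 plans detection by the program as well as comparison with the diary, and it tests the program against examiner notes. The sheet also has timed daily-life entries and a free-text column, and a relative may fill it in. Care episodes can therefore be located and set against the program's output. In a 10-patient validation study, detection of passive movement is itself under evaluation.

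Much of this stands. A reader might infer that carer-moved arms will necessarily be counted as patient activity, or that the diary comparison is impossible. The documents support neither reading: the program may catch some or all of such movement, and a coarse comparison by episode can be made. Nor does the activity column label movement as active; it names the occasion.

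A reader might also take the criterion "able to sit on a wheelchair during at least three hours" to mean that up to 12 of the 15 recorded hours (15 − 3 = 12, or 80%) are spent out of the chair. That is not supported. The criterion is a minimum capacity for entry and says nothing about chair time at home. Likewise, the protocol gives no basis for expressing the error as a share of active time, for calling passive movement the main source of error, or for expecting it to reverse the relation with function.

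What the reply does not answer is the absence of a prompted record, on home days, of who moved the arm. The wheelchair sensor may help with motion caused by the chair, but the protocol does not say how it is used. It cannot alone identify a carer-moved arm or an empty chair.

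**Conclusion.** The point holds as a mismatch within the protocol. Section 18.2 relies on the diary for information that neither the sheet nor the instructions request. Carer-induced movement at home may be misclassified as activity, and the home exclusion cannot be properly verified against the diary as it stands.

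The absence of the fields is certain from the text. The size of the effect cannot be derived from it. The 3% to 13% of recorded time is an illustration that assumes 30 to 120 minutes a day of carer-moved arm time with none of it detected. The conclusion does not depend on that range. This is an inexpensive correction that should be made, not a flaw that invalidates the study.

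**What to change.** Before first use, add two prompted entries to Appendix 1, and to the instructions in sections 8.1 and 9: arm moved by another person (from/to), and in or out of the wheelchair (from/to). In section 18.2, name these periods as the reference for the home exclusion. Report home activity with and without washing and dressing periods as a sensitivity check.

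If the diary is left unchanged, remove it as comparator in section 18.2 and state that home exclusion rests on the program as tested on assessment days.

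The cost of the first option is a revised sheet, brief training and slightly more diary burden for the family. The second needs only a change of wording, but leaves the home exclusion without a reference of its own.

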## 8.2. PROGRESS OF THE EVALUATION

In the controlled environment, there are the following tests:

- Tests of strength
  - *Hand Grip* – dominant then non-dominant hand, three trials
  - *Pinch* test - dominant then non-dominant hand, three trials
- Quantified tests (with scores)

- *Box and block* test - dominant then non-dominant hand, three trials
- Minnesota test (variant) - dominant then non-dominant hand, three trials
- Moviplat - dominant then non-dominant hand, three trials
- Continuous typing a phrase on the computer: "*Les pompiers sont partis de la caserne avec leur camion rouge*" ("The fire brigade left the fire station with their red truck") - dominant hand, three tries
- Buttoning up a jacket – (device on the dominant hand), one try
- Free movements
  - Having lunch (device on the dominant hand)
  - Brush the teeth (device on the dominant hand)
  - Writing the phrase (device on the dominant hand) "*Les pompiers sont partis de la caserne avec leur camion rouge*" ("The fire brigade left the fire station with their red truck ")

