## 9. DESCRIPTION OF THE EVALUATION

**Actimyo** (Bere et al. 2011) is a system which aims to measure the physical activity of a patient from the extraction of the data recorded by sensors fixed on the limb and on the electric wheelchair.

It consists of one or more sensor blocks, a sensor/PC interface (wheelchair box) and the software of data acquisition/decoding installed on the PC. Each block consists of an accelerometer, a gyroscope, and a magnetometer, measuring respectively the acceleration and the angular speed in the magnetic field in three spatial axes. It is fixed on the limb for which we plan to study the movement. The sensor/PC interface synchronizes with sensor blocks and can centralize the data. The software can decode the data and recover them as Excel files. All

---

 Elodie Béré, Mark Benoit, David Vissière, Jacques Duchêne, [name], Laurent Servais, *Actimetry & Neuromuscular Disorders: a system suitable for upper limb evaluation*, Myology 2011

connections Sensors ↔ Interface ↔ PC are through Bluetooth radio transmission. The sensors and the interface box are autonomous from the point of view of energy. The functioning will be based on rechargeable batteries at night.

The sensor block will be protected by a plastic box as shown and worn as a watch on the wrist of the dominant limb on Monday, Wednesday, Friday and Sunday, and on the non-dominant limb on Tuesday, Thursday and Saturday. Another sensor block may be placed on the wrist of the non-dominant limb. The plastic box is small and light enough (38 g, 43/33/20 mm) not to intervene with the subject's movement. [Appendix 2]

**Handgrip** is a tool to measure the strength of the palmar grip of the subject. The patient will grasp as hard as possible the handle of Handgrip, first with his dominant and then with his non-dominant limb. Three consecutive trials will be done on each side. [Appendix 3]

**Pinch test** is a tool to measure the strength of the thumb-index pinch. The patient will pinch the measurement tool as strongly as possible with his dominant and non-dominant limb. Three consecutive tries will be realized on each side. [Appendix 4]

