**Box and Block Test (BBT)** is a manual dexterity test, originally developed for adults with cerebral palsy (Mathiowetz et al., 1985). The test consists of a box separated on two equal compartments; one of them contains a number of wooden blocks. The patient will be asked to grab each block with one hand and put it into the empty compartment. The score corresponds the number of blocks moved to the other side during sixty seconds. The test is performed three times, alternating dominant and non-dominant limb. [Appendix 5]

**Minnesota manual dexterity test** is a standardized test, which can assess the ability of the subject to move discs for small distances. It is commonly used for the evaluation of professional competence, for the disability assessment (Gloss et al., 1982), and rehabilitation. We propose seven various wooden discs, coloured on one side, arranged in inverted "V". The patients have to turn the discs on the coloured side, starting with his dominant side, then on the uncoloured side for sixty seconds. The score corresponds the number of returned discs. Three tries will be realized alternately on each side starting with the dominant hand. [Appendix 6]

**Moviplat** is a device developed by the Institute of Myology and has been validated for DMD patients (Servais et al., 2010). The device includes two platforms. The aim is simply to touch alternately each platform. These platforms are connected to the force sensor, which directly measures the developed strength. A counter indicates the number of contacts and a chronometer

counts the time on a selected duration. The score corresponds the number of pair contacts for thirty seconds. Three tries will be realized alternately on each side starting with the dominant hand. [Appendix 7].

**Typing a sentence on the computer keyboard** is a task of daily life. We ask a subject to type with one finger of the dominant hand as many times as possible for sixty seconds the following sentence (no punctuation, no capital letters, and no corrections): "*Les pompiers sont partis de la caserne avec leur camion rouge*" ("The fire brigade left the fire station with their red truck."). The score corresponds the number of characters (including spaces) typed. The test will be done tree times.

**The buttons of the jacket:** The patient will be asked to button up a jacket, the sleeves of which have been previously strung, for sixty seconds. The score corresponds the number of buttoned buttons.

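### Clinic reference recordings of the daily-life tasks are specified for the dominant hand only, but 6 of 14 home days are on the non-dominant wrist, and the only dressing task recorded is buttoning

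*Protocol*

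**What the plan says.** Section 18.2 of the Protocol, under movements in the free environment, plans for the activity periods a "recognition of a particular task with the help of recordings in the controlled environment (ex: teeth brushing, eating, getting dressed"). The clinic recordings thus serve as the reference for what the home sensor records.

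Section 8.2 fixes how the clinic recordings are made. For eating it says "Having lunch (device on the dominant hand"), for tooth brushing "Brush the teeth (device on the dominant hand") and for dressing "Buttoning up a jacket – (device on the dominant hand), one try". Writing carries the same dominant-hand note, and typing is done with the dominant hand. Box and Block, Minnesota and Moviplat are done on both sides.

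Section 9 assigns the home sensor to the dominant wrist on Monday, Wednesday, Friday and Sunday, and "on the non-dominant limb on Tuesday, Thursday and Saturday". It adds: "Another sensor block may be placed on the wrist of the non-dominant limb". It does not say when or in which setting. The later part of section 9, on use outside the Institute, sends the patient home with one wrist sensor and one wheelchair sensor.

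Section 9 describes the dressing-type task as follows: "The patient will be asked to button up a jacket, the sleeves of which have been previously strung, for sixty seconds".

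**The concern.** A clinic recording helps to recognise a home task only if it shows what the home sensor would see during that task. In a largely one-handed task such as tooth brushing, the other wrist may be still, or may be supporting. Section 9 itself notes that these patients use many adaptation strategies, so the movement of one wrist cannot be presumed from that of the other.

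For the non-dominant home days, the plan therefore asks for recognition without a same-wrist reference. For dressing, the reference covers one component of the activity. Validation of the recorded data is one of the three aims in section 4. A recognition result that mixed days with and without a matching reference would be hard to interpret: poor recognition could come from the device, the algorithm or the missing reference.

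**Working it through.** **Inputs**
- Home period: 14 days (section 1; D0 to D14 in Table 1).
- Recording time: about 15 hours per day (section 8.1 and Table 1).
- Home wrist: dominant on 4 weekdays, non-dominant on 3 (section 9).
- Clinic hand for each task: section 8.2.

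The Protocol gives no figure of its own to reproduce here.

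**Step 1. Days and hours.** Fourteen consecutive days contain each weekday exactly twice, so the count does not depend on the starting day.
- Non-dominant days: 3 × 2 = 6, and 6 / 14 = 42.9%.
- Dominant days: 4 × 2 = 8.
- Hours: 6 × 15 = 90 non-dominant and 8 × 15 = 120 dominant, out of 14 × 15 = 210.

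**Step 2. Sensitivity to the visit days.** If D0 and D14 are counted differently, the starting weekday matters slightly.
- 13 days: 5 or 6 non-dominant days (5/13 = 38% to 6/13 = 46%).
- 15 days: 6 or 7 non-dominant days (6/15 = 40% to 7/15 = 47%).

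**Step 3. Tasks against clinic references.**

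| Task | Named in 18.2 for recognition | Clinic recording, dominant | Clinic recording, non-dominant |
|---|---|---|---|
| Tooth brushing | yes | yes | not specified |
| Eating | yes | yes (lunch) | not specified |
| Dressing | yes | buttoning only, sleeves already on | not specified |
| Writing, typing | no | yes | not specified |
| Box and Block, Minnesota, Moviplat | no | yes | yes |

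For typing and for the two-sided tests, section 8.2 states the hand that performs the task. I take the sensor to be on that hand.

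**Reading.** Every task named for recognition lacks a specified non-dominant reference. The tests that do have a two-sided recording are not among the tasks named. For dressing, the dominant-wrist reference is one 60-second try at one component, repeated at each visit.

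**The case against.** The strongest case on the other side has four parts.

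- **The wording is loose.** Section 18.2 speaks only of help from the clinic recordings. It does not prescribe same-wrist matching or exclude other information. This stands. A reader might infer that recognition on non-dominant days must fail or produce false matches, but the documents do not support that. Eating and dressing can involve both hands, so the non-dominant wrist need not be idle.
- **No recognition rate is defined.** The Protocol names no rate, no pooling over wrists and no success threshold, and does not say that recognition applies to every home day. This also stands. A reader might go on to calculate how far a pooled rate would be diluted, but any such figure would rest on invented inputs, and I give none.
- **The diary helps.** The Appendix 1 form has a field for the hand, so each day can be assigned to a wrist. Sections 8.1 and 9 ask for start and end times of activities, dressing among them. This mitigates the gap in part, because it gives labelled home data on both wrists. But the labels are self-reported or written by a relative, on a form laid out in one-hour rows. They do not replace an observed clinic recording, which is the reference that section 18.2 names.
- **The analysis plan could handle it.** Stratifying by wrist or restricting the days is ordinary analysis-plan detail. That is true, but no analysis plan can create a clinic recording that was never made. Section 9 permits a second block but does not commit to it, and section 8.2 mentions only the dominant hand for these tasks.

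A reader might also infer that dressing is never recorded in clinic. It is recorded in part: buttoning is recorded with the device at both D0 and D14.

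**Conclusion.** The point holds as a gap in data acquisition. On 6 of 14 home days (43%, about 90 of 210 hours), the Protocol specifies no same-wrist clinic recording for any task that it names for recognition. On those days recognition cannot be expected to work as well, and cannot be checked against a matching recording. Putting on a garment has no clinic reference on either wrist; only buttoning does.

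This rests on three assumptions: the weekday schedule is followed, about 15 hours are recorded each day, and the optional second block is not used in clinic for these tasks. If it is used there, the wrist gap closes and only the dressing point remains.

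The consequence is limited to one descriptive item. The clinic correlations and ICC, the activity and inactivity percentages, the histograms and the comparison of profiles with functional ability do not depend on it. The change is worth making because it costs little and cannot be made after the visits.

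**What to change.** 1. In section 8.2, state that the second sensor block already permitted in section 9 is worn on the non-dominant wrist during lunch, tooth brushing, writing, buttoning and typing, at both D0 and D14.
2. In section 18.2, state that home recordings are matched to clinic recordings from the same wrist, with the wrist taken from the diary's hand field, and that recognition is reported separately by wrist.
3. If no second block is used, restrict clinic-based recognition to the 8 dominant-wrist days.
4. In section 18.2, state that the dressing-type task with a clinic reference is buttoning. Dressing can stay in the diary as a logged activity.

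**Cost.** Items 2 and 4 are wording changes. Item 1 needs a second block available at the visits and worn during tasks already scheduled; it adds no visit or test and leaves the home wearing schedule as it is. Item 3 needs no equipment, but 43% of home days (about 90 hours, leaving about 120) drop out of this one analysis.
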